## Methods

### Setting

This randomized-control trial (RCT), pilot study was embedded within a large-scale, National Institute of Mental Health-funded study, the *Interagency Collaborative Teams to Scale-Up Evidence Based Practice* (ICT) [25]*.* The ICT study was a system-wide, mixed-methods implementation study focused on understanding inner and outer context factors associated with the effective implementation and sustainment of SC delivered to child welfare-involved parents, in a large, diverse child welfare service (CWS) system. The ICT study components (which include an assessment of the feasibility and acceptability of SC/SC+, the impact of service attrition on study outcomes, and fidelity to the intervention) serve as a foundation for the current pilot RCT.

The scale up of SC occurred across multiple community-based organizations (CBOs). These CBOs are contracted by CWS to deliver parent training, such as SC, via an in-home service delivery platform. Families involved with CWS are referred to the CBOs to receive SC because they had children between the ages of 0 and 11 and child neglect was the primary referral reason. As an EB curriculum, SC is structurally and behaviorally prescriptive on how its curriculum is to be delivered to the targeted parents by the home visitors. Most often, parents participate in the SC curriculum individually with the home visitor. Parent participant eligibility criteria for the ICT study were (1) at least 18 years of age; (2) were referred for child neglect; and (3) had at least one child in the family under age 12. Over 90% of eligible parents enrolled in the ICT study.

### Design

The pilot study is divided into two phases. During phase one, the first year of the study, community and academic partners collaborate to develop a detailed evaluation plan. The evaluation centers on the effective implementation of SC+ and measurement of relevant outcomes during phase two of the project—the RCT, pilot study. Components of phase one include (1) a community needs assessment, (2) refining the target population, (3) designing the evaluation plan, (4) determining screening and outcome measures, (5) conducting focus groups with key stakeholders, including DV providers and Latinx survivors, to assure that the chosen interventions and screening and assessment tools are culturally appropriate for the target population, and (6) ensuring the proper training of direct service staff. For phase two, the RCT pilot study will enroll at least 160 parents either into SC or SC+, allocating a minimum of 80 parents per condition. Parents will be randomized to SC or SC+ and within home visitor, such that every other eligible parent will be assigned to SC or SC+ within home visitor. The nested structure will be accounted for in multi-level analyses, see Fig. 1 (SafeCare+ study flow diagram).

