### Eligibility criteria

Participants will be included in the RCT pilot study if the following criteria are met: (1) currently receiving SC services, meeting ICT inclusion criteria; (2) a primary caregiver identifying as Latinx; (3) over 18 years of age; and (4) at risk for DV. The criterion for risk of DV was intentionally set to be broadly inclusive of families who are struggling with psychological violence. Clients will be excluded from participation if there are immediate safety risks in the family.

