### Measures

All measures are client-reported and will be collected via a secure, web-based data entry system, on an internet-enabled tablet that service providers bring to each visit. At the end of each SC or SC+ visit, providers activate the participant survey by logging into the secure web-based data entry system on their assigned tablet computer and selecting the appropriate client identifier (a number randomly generated by the secure system). Once the survey has been activated, the service provider will give the client the tablet computer to complete the measures privately. In the infrequent circumstance that two parents are simultaneously participating in services, the assessments are completed by each, separately, while the other parent is engaged with the home visitor. All measures are available in both English and Spanish.

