#### Screening measures

*Hurt*, *Insult*, *Threaten*, *Scream* (HITS) [30] is a 4-item instrument for DV screening. Items ask respondents how often their partner physically hurt, insulted, threatened with harm, and screamed at them. A score of 10.5 (range 4 to 20) was demonstrated to reliably differentiate victims of domestic abuse from family practice patients. The current pilot study includes parents who report a score of 7 or higher.

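### The allocation called randomized is alternation within home visitor, so every assignment after a visitor's first is predictable to the person who delivers both arms

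*Protocol article*

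**What the plan says.** The Design section states: "Parents will be randomized to SC or SC+ and within home visitor". The same sentence then defines how this is done: "every other eligible parent will be assigned to SC or SC+ within home visitor". No random sequence or concealment step is described, nor how a visitor's first parent is assigned or who issues assignments.

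Three other places show how close the visitor is to entry:
- Setting describes SafeCare as prescriptive on "how its curriculum is to be delivered to the targeted parents by the home visitors". Since alternation runs within visitor, each visitor delivers both SC and SC+.
- Eligibility criteria require that the parent is "currently receiving SC services, meeting ICT inclusion criteria". The visitor can therefore know the family before trial entry.
- Measures says the provider brings the tablet and activates each survey, which the client then completes privately.

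The Discussion makes showing the effectiveness of the healthy relationships (HR) curriculum a primary aim and expects the results to supply efficacy data for a system-wide trial.

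**The concern.** Random allocation protects a comparison only if nobody who can affect entry can foresee the next arm. Alternation lacks that property: once one assignment is known, the next follows. Here the person who necessarily knows the last assignment is the visitor who is delivering it.

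The article itself supplies a prognostic cue that could matter. The Discussion says the HR curriculum lengthens services by about two months, so some SC+ parents may not receive all, or any, of it before the child welfare time limit. A visitor may have a fair idea which families will run out of time. Bringing a family forward or delaying it, even with good intentions, would make the arms differ from the start. At stake is the between-arm comparison that is meant to inform the decision on a definitive trial.

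**Working it through.** **1. Label against rule.** A randomized sequence is one that cannot be worked out from earlier assignments. The stated rule gives SC, SC+, SC, SC+ and so on (or the reverse) within each visitor. The two are incompatible, so this is a stated rule without the property claimed for it, not a detail left to a fuller document.

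**2. The plan's own figure.** The only figure is 160 parents (at least 80 per arm), called adequate for a medium Cohen's d. No alpha or power is given, so there is nothing to reproduce. Taking medium as d = 0.5 and a two-sided 5% test, before clustering or dropout, 126 parents give 80% power, 170 give 90%, and 160 give 88.5%. The sample size is not disputed here.

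**3. How much is predictable.** Let V be the number of visitors (not in the document; 10, 20 and 40 assumed) and N = 160.
- Share fully determined = (N − V)/N.
- With a 50:50 guess on each visitor's first parent, expected share guessed correctly = 1 − V/(2N).

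| V | Fully determined | Guessed correctly |
|---|---|---|
| 10 | 150/160 = 94% | 97% |
| 20 | 140/160 = 88% | 94% |
| 40 | 120/160 = 75% | 88% |

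If every visitor's starting arm is also fixed and known, all 160 are determined.

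**4. What steering could do (hypothetical).** Suppose parents entered when SC+ is expected differ by +e SD in prognosis, and those entered when SC is expected by −e SD. There is no true effect and no steering on a visitor's first parent. Then spurious difference = 2e × (N − V)/N.
- e = 0.2: 0.4 × 0.9375 = 0.375; 0.4 × 0.875 = 0.35; 0.4 × 0.75 = 0.30 SD.
- e = 0.1: 0.19, 0.175 and 0.15 SD.

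With 80 per arm and SD 1, the standard error is √(2/80) = 0.158. A simulation (1,000 runs per setting, independent outcomes, nominal 5% test) agrees with these differences. Its false-positive rates for V = 10/20/40 were about 67%/60%/46% at e = 0.2 and 23%/20%/16% at e = 0.1. Without steering they were 3% to 6%, as expected.

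**5. The alternative under the same assumptions.** With random blocks of 2, 4 and 6 within visitor, a visitor who remembers past assignments and guesses the arm that is behind is right 69%/69%/67% of the time. At e = 0.2 the spurious difference is 0.16/0.15/0.14 SD and the false-positive rate about 18%/16%/13%. Simple randomization gives 50% correct guesses, a difference of about 0, and 4% to 7%. Random blocks more than halve the exposure but do not remove it.

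**The case against.** The article condenses a fuller protocol, and its Fig. 1 is not shown, so more may be specified elsewhere. That would answer an omission. It does not answer an explicit rule that is deterministic.

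The other objections limit how far the point can go, and they stand:

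- **Who screens and excludes.** A reader might infer that the visitor decides eligibility. The document does not say so. The screening score is the client's own report against a fixed threshold ("The current pilot study includes parents who report a score of 7 or higher"), on a survey completed privately. The safety criterion, "Clients will be excluded from participation if there are immediate safety risks in the family", names no assessor. Only treatment delivery and survey activation are documented; influence on entry is a reasonable possibility.
- **Arm sizes.** A reader might infer that alternation misses the target because odd caseloads leave one arm larger. The plan commits to "allocating a minimum of 80 parents per condition" within a total of at least 160, so enrolment can continue. A visitor's imbalance is at most one parent, and incomplete random blocks would do no better.
- **Split households.** A reader might infer that couples always land in opposite arms. That needs both parents to be eligible, enrolled consecutively and counted separately. The article says only "In the infrequent circumstance that two parents are simultaneously participating in services" and does not say that both are entered. The issue is conditional and cannot be sized.
- **Analysis.** It would be too strong to say that analysis cannot help. The CTS2 and CES-D are measured at baseline and the models include covariates, so bias through measured severity could be reduced. Selection on unmeasured prognosis would remain.

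**Conclusion.** The point holds in this form: the Design section labels alternation as randomization, and every assignment after a visitor's first is predictable to the visitor, who delivers both arms. This follows from the text and needs no assumption about who formally issues assignments.

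The shares in the working depend on an assumed number of visitors. The bias and error rates also depend on an assumed degree of steering, so they are purely illustrative. They do not show that steering occurred. They show that modest steering (0.1 to 0.2 SD) could produce 0.15 to 0.38 SD, which is 30% to 75% of an effect of d = 0.5. Pilot status does not excuse this, because the comparison is meant to supply efficacy data. It should be corrected before further parents are entered.

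**What to change.** - **Parents still to be enrolled** (the Data Availability statement says recruitment is ongoing): use a computer-generated random sequence stratified by home visitor, with randomly varying block sizes. Conceal it, and release each assignment only after eligibility, consent and baseline measures are recorded. Do not disclose block sizes to visitors, who will still know their own past assignments.
- **Parents already alternated:** describe them as quasi-randomised, report their baseline balance, and give a sensitivity analysis by allocation method. If recruitment has ended, only this part applies.
- **Households:** if two parents of one household are both enrolled, allocate them together.

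Cost: a protocol amendment and modest programming, since the article describes the web system for data entry and client identifiers, not for allocation. The sample will have been allocated by two methods, and slight chance imbalance within visitors must be accepted.

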**Fig. 1 Fig1:**
[figure not shown]
SafeCare+ study flow diagram

### Eligibility criteria

Participants will be included in the RCT pilot study if the following criteria are met: (1) currently receiving SC services, meeting ICT inclusion criteria; (2) a primary caregiver identifying as Latinx; (3) over 18 years of age; and (4) at risk for DV. The criterion for risk of DV was intentionally set to be broadly inclusive of families who are struggling with psychological violence. Clients will be excluded from participation if there are immediate safety risks in the family.

#### Ethical considerations

Participants providing data in the study are service clients receiving family preservation/family reunification services (i.e., SC via home visitation) through partnering CBOs in the CWS system. These services are most often targeted at concerns over child neglect, and services are designed to strengthen the capacity of families to care for young children. Parental participation in the research study is voluntary, and parental data is maintained separate from CWS records. Parental declination to participate in the research study has no impact on service receipt—clients will receive CWS services independent of participation in the study.

### Interventions

#### Control group: SafeCare

SafeCare (SC) is an EB parenting curriculum, delivered via home visitation, for parents with preschool or school-age children who are at risk of or have been reported for child neglect, physical abuse, or both. SC targets improvement in skills related to home safety, health, and parent-child interaction [26]. These modules include a baseline assessment, training in knowledge and skills, and follow-up assessments to monitor change. Delivery of the program is based on the principles of behavioral analysis—service providers are trained to model skills, engage in ongoing measurement of observable behaviors, and to give constructive feedback during skills practice. SC program completion typically takes 18 to 20 home visiting sessions over 6 months. A number of studies attest to SC effectiveness and provide evidence on improved parental outcomes, including better management of their child’s health, increased home safety, and more positive and sensitive parent-child interaction [26–28]. In addition, SC has been demonstrated to be efficacious for reducing CWS recidivism relative to usual care [29]. Participants randomized to the control group will receive the EB, SC as usual.

#### Experimental group: SafeCare with Healthy Relationships (SafeCare+)

Participants randomized to the experimental group will receive SC+, an enhanced version of the SC program, which includes the healthy relationships (HR) curriculum, specifically designed for early intervention with family violence. The HR curriculum is intended to help parents recognize abusive patterns, develop healthier relationships, and improve communication skills with a range of adults, including intimate partners, family members, friends, and with their children. The HR module (1) provides information about how relationships can affect health and well-being for parent and child; (2) reviews qualities of healthy and unhealthy relationships; (3) assesses the type and quality of the parent’s important relationships; (4) empowers the parent to be an active participant in improving the quality of their personal relationships; and (5) teaches communication, problem-solving, and interpersonal skills to facilitate enhancing the quality of their personal relationships. The HR module is delivered in a similar skills-based format as other SC components, with ongoing measurement and feedback in areas of communication, problem solving, and interpersonal interactions.

### Feasibility outcomes

Acceptability of the intervention will be examined in both phases of the study. First, focus groups with the target population participants will determine the perceived fit of the intervention for the population. Focus groups will also provide information regarding the variety of experiences, barriers, and strengths that exist within various sub-groups of the target population (e.g., younger and older parents, recent immigrants). This information will be used to design and test various approaches to service delivery to meet the varied needs of the target population and to determine the feasibility for expanding the target population to include a prevention base for families at risk of DV. Second, satisfaction will be established by program participants on all intervention components. In addition to acceptability, SC+ limited effectiveness will be ascertained by comparisons between the experimental and control groups on key outcome measures, set to achieve at minimally medium effect size. Finally, practicality (i.e., perceived sustainability within the existing infrastructure) will be explored at the conclusion of the study via interviews with providers and service system leadership.

### Measures

All measures are client-reported and will be collected via a secure, web-based data entry system, on an internet-enabled tablet that service providers bring to each visit. At the end of each SC or SC+ visit, providers activate the participant survey by logging into the secure web-based data entry system on their assigned tablet computer and selecting the appropriate client identifier (a number randomly generated by the secure system). Once the survey has been activated, the service provider will give the client the tablet computer to complete the measures privately. In the infrequent circumstance that two parents are simultaneously participating in services, the assessments are completed by each, separately, while the other parent is engaged with the home visitor. All measures are available in both English and Spanish.

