### Data collection points for outcome measures

Data collection for SC/SC+ fidelity will be conducted at each session of the intervention, throughout the course of service delivery. The CES-D is assessed at intake into SC, at the end of the intervention, and at the end of the study. The CTS-2, WAI, RSE, and relationship status measures are assessed at the beginning and conclusion of receiving the intervention (i.e., the HR curriculum, or the comparison time frame for the control condition). HR satisfaction is assessed at the conclusion of receiving the intervention, see Fig. 3 (SPIRIT figure for SafeCare+ trial for data collection timings).

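### The CTS2, RSE, WAI and relationship status baseline is not fixed before the first Healthy Relationships content, and the stated survey procedure allows it to fall after that content in SC+ only

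*Protocol article*

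**What the plan says.** **Procedure within a visit.** The Measures section of the protocol article covers every instrument: "All measures are client-reported and will be collected via a secure, web-based data entry system, on an internet-enabled tablet". It then says when the survey opens: "At the end of each SC or SC+ visit, providers activate the participant survey by logging into the secure web-based data entry system". No exception is made for baseline.

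**Timing across visits.** Under Data collection points for outcome measures: "The CTS-2, WAI, RSE, and relationship status measures are assessed at the beginning and conclusion of receiving the intervention". The parenthesis that follows defines the intervention for this purpose: "i.e., the HR curriculum, or the comparison time frame for the control condition". The depression scale has a different, earlier anchor: "The CES-D is assessed at intake into SC, at the end of the intervention, and at the end of the study".

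**Other relevant text.**
- Under Eligibility criteria, participants must be "currently receiving SC services, meeting ICT inclusion criteria", so they have home visits before HR begins.
- The description of the experimental arm says that the HR module, among other things, "reviews qualities of healthy and unhealthy relationships" and teaches communication and problem-solving.
- Under Outcome measures, 13 RSE items were retained because they bear on HR content.
- Quantitative analyses lists four dependent variables. Change in CTS reports of domestic violence and change in RSE are two of them; WAI is not listed.
- The Discussion warns that some parents assigned to SC+ may receive none of the added curriculum, because services run out of time.

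**The concern.** A home visitor who follows both rules literally would open the baseline survey at the end of the first HR visit. The SC+ parent would then answer after some HR content, and the control parent after an ordinary SC visit. The pre-intervention value would be post-exposure in one arm only.

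For RSE, whose items were chosen to match HR content, an early gain would be counted as baseline and subtracted from the effect. For CTS2, teaching about abusive patterns might change what a parent reports. Two of the four dependent variables use this baseline. Statistical adjustment for a baseline that treatment has already moved does not remove the bias, and the lost pre-exposure value cannot be recovered at analysis.

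There is a second difficulty. For an SC+ parent who never starts HR, the beginning of HR does not exist. The baseline date is then undefined, and among parents assigned to SC+ this falls on those whose services ended early.

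**Working it through.** **Step 1: which visits satisfy both rules?**

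| Candidate baseline in SC+ | End-of-visit rule | Beginning-of-HR rule | Before HR content? |
|---|---|---|---|
| End of first HR visit | Satisfied | Satisfied, the more literal reading | No |
| End of last SC visit before HR | Satisfied | Satisfied on a looser reading | Yes |
| Intake into SC | Satisfied | Not satisfied; this anchor is given to CES-D only | Yes |

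Two candidates remain. The first is the more natural, because a visit before HR starts precedes receipt of HR, and because the article uses an intake anchor explicitly where it wants one. The text does not choose between them.

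**Step 2: the plan's own figure.** The Sample size section says that 160 parents (80 per arm, from Design) suffice for a medium Cohen's d. Alpha, power and the value of d are not given, so 160 can be neither reproduced nor refuted. Assuming d = 0.50, SD 1, two-sided 5%, and no clustering or dropout:

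- noncentrality = d × √(n/2) = 0.50 × √40 = 3.16
- two-sample t-test on 158 degrees of freedom: power 88.2%

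**Step 3: illustration of the loss on RSE.** Let f be the share of the final effect already present at a post-session baseline. The documents give no value for f; the values below are assumptions. The change-score effect is 0.50 × (1 − f).

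| f | Effect in change score | Noncentrality | Power |
|---|---|---|---|
| 0 | 0.500 | 3.16 | 88.2% |
| 5% | 0.475 | 3.00 | 84.8% |
| 10% | 0.450 | 2.85 | 80.8% |
| 25% | 0.375 | 2.37 | 65.4% |

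A normal approximation gives figures 0.4 to 0.6 points higher (88.5%, 85.2%, 81.2%, 66.0%).

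**Step 4: if the model adjusts for baseline.** With baseline-outcome correlation ρ and equal variances, the adjusted effect is 0.50 × (1 − ρf) and the residual SD is √(1 − ρ²). At an assumed ρ = 0.5 the SD of the change score is √(2 × (1 − 0.5)) = 1, so this is on the same scale as Step 3. By the normal approximation:

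- f = 0: effect 0.500, power 95.5%
- f = 10%: effect 0.475, power 93.4%, a loss of 2.1 points (7.3 points with change scores)
- f = 25%: effect 0.4375, power 89.2%, a loss of 6.3 points (22.5 points with change scores)

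Adjustment halves the bias at this correlation but does not remove it.

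**Step 5: CTS2.** The baseline asks about the frequency of concrete acts over the past 6 months. One session cannot alter that history; it could only alter reporting. The documents give nothing from which to size or sign that shift.

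**The case against.** The strongest objection is that no sentence places the baseline after an HR session. The end of the preceding SC visit meets both rules and is a clean baseline, and Fig. 3, which carries the collection timings, is not shown in the text available for this review. This stands. A reader might infer that the SC+ baseline is definitely post-exposure; the documents do not support that, and the point is limited to what they permit.

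Second, the first HR session may be largely assessment. SC modules are described as including a baseline assessment, training and follow-up assessments, and HR is delivered in a similar format. This also stands in part: the first session is not shown to be mainly teaching, so f could be small. But those are assessments within the module, while the client survey opens when the visit is over.

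Third, a reader might infer that CTS2 and RSE are biased in opposite directions, with an exaggerated CTS2 fall in SC+. That needs HR to raise reporting at baseline. CTS2 asks about concrete acts and does not ask parents to label them as abuse, so the direction is speculative.

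Fourth, WAI is not a listed dependent variable, so the consequence there is secondary. CES-D is taken at SC intake and is unaffected.

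Fifth, an article condenses the protocol, and which form opens at which visit is often left to the full document. That is fair as to detail. What remains is that the article does state a procedure and a baseline anchor, and in combination they allow a baseline after exposure.

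**Conclusion.** The point holds as an ambiguity with a real risk attached. The two timing rules do not secure a baseline before HR content, and their most natural combined reading puts it after the first HR session in SC+ only. It should be fixed as a cheap improvement; it does not show that the trial's data are contaminated.

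If the baseline is taken late, the expected consequence is attenuation of the RSE change. Power would fall from about 88% to about 85%, 81% or 65% for absorbed shares of 5%, 10% or 25%, and by less with baseline adjustment. These figures rest on an assumed d of 0.50, assumed shares, 80 per arm with no dropout, and no clustering by home visitor. No size or direction can be given for CTS2. The missing baseline date for SC+ parents who never start HR does not depend on any of these assumptions.

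**What to change.** Under Data collection points for outcome measures, state that CTS2, RSE, WAI and relationship status are completed before any HR content is delivered, at the same point in both arms. The preferable point is the end of the SC visit at which HITS eligibility is confirmed, before the arm is disclosed. That also gives a dated baseline to SC+ parents who never reach HR. Fig. 3 should be checked so that it agrees.

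The cost is a clause in the protocol and a change to when the tablet survey opens. No visit is added, because parents are already receiving SC. There are two downsides: a longer survey at that visit, and possibly a longer gap between baseline and the start of HR, which the documents do not allow one to estimate. Collecting before disclosure gives limited extra protection, since assignment alternates between eligible parents within home visitor and can be anticipated. The main gain is that the baseline precedes exposure.
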